### Session 2 (week one)

2.10

At this session, participants in both groups will have their running gait assessed via 2D video. Participants in the intervention group will be provided with real‐time feedback on their running step length. If required, modifications will be made to the step rate feedback for participants in the intervention group to help achieve the desired step length. Participants will also have an opportunity to seek any clarification regarding their strengthening program and symptom management advice.

### Session 3 (week two)

2.11

At this session, primary and secondary outcome measures will be collected, and participants will be instructed on the next 2 weeks of their running and strengthening program. Each participant will have the progression of their running program reviewed with [name] with any progressions dependent on their current symptoms during and post‐run. Progression of their strength program will depend on their progress and ability to have achieved dosages in their current program, this will be individually discussed with [name]. All participants will have their running gait assessed via 2D video, and participants in the intervention group will be provided with real‐time feedback on their running step length.

### Session 4 (week four)

2.12

As per session two, participants will have primary and secondary outcome measures collected. Participants will be instructed on the next 4 weeks of progressions of their running and strengthening program. All participants will have their running gait assessed via 2D video, and participants in the intervention group will be provided with real‐time feedback on their running step length.

### Session 5 (week eight)

2.13

Primary and secondary outcome measurements will be collected, and all participants will have their running gait assessed via 2D video at the conclusion of the trial.

### Outcome measures

2.14

The primary outcome measure will be the University of Wisconsin Running Injury and Recovery Index (UWRI). The UWRI is a nine‐item running specific patient‐reported outcome measure that relates to both running progression and symptom surveillance. It has been found to have acceptable internal consistency (*α* = 0.82) and test–retest reliability (ICC: 0.93) when assessing running ability following a running‐related injury [12]. Scores range from 0 to 36.

The secondary outcome measures will be as follows.

#### Exercise Induced Leg Pain Questionnaire—British Version

2.14.1

The Exercise‐Induced Leg Pain Questionnaire (EILPQ‐Br) has been found to have excellent internal consistency (intraclass correlation coefficient [ICC]: 0.92–0.94) and test–retest reliability (ICC: 0.987–0.995) across patients with exercise‐related lower leg pain [16]. The EILPQ‐Br questionnaire comprises 10 items, scored on a five‐point Likert scale from 4 (no difficulty) to 0 (unable to do), there is also a ‘non‐applicable’ category. Scores range from 0 to 40.

#### Global rating of change scale

2.14.2

Participants will be required to rate their self‐perceived improvement on a 15‐point Global Rating of Change Scale with −7 representing ‘a very great deal worse’ and +7 representing ‘a very great deal better’. Global rating of change scales have been shown to be a valid and reliable way of evaluating self‐assessed clinical progress (ICC 0.90) [17].

#### Adherence to exercise for musculoskeletal pain tool (ATEMPT)

2.14.3

Participants will be required to rate their adherence to exercise across six items relating to communication with expert; targets; how exercise is prescribed; patient knowledge and understanding; motivation and support; and psychological approach and attitude.

The Adherence to Exercise for Musculoskeletal Pain Tool (ATEMPT) has been shown to be valid and reliable in the measurement of adherence to exercise in musculoskeletal pain presentations [18].

#### Worst pain experienced during a run—NPRS

2.14.4

Participants will be required to rate their pain on an 11‐point NPRS with 0 representing ‘no pain’ and 10 representing ‘the worst pain imaginable’. The NPRS has been shown to be valid and reliable in measuring changes in both acute and persistent pain states [19]. Participants will record their pain on the NPRS immediately following a run to indicate the worse level of pain they experienced within their run.

#### Weekly run volume

2.14.5

Participants will record the distance of each run with the use of their Garmin running watch. Total weekly volume for each participant will be downloaded by [name] and documented in an excel spreadsheet (Microsoft Corporation, Washington, USA). Running volume will be recorded as kilometres per week.

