#### Load management advice

2.6.1

Participants will be instructed to ensure a pain level of no more than a 2 out of 10 during a run, reported on a NPRS. At the commencement of the trial an individual run program will be discussed with [name] ([name]), with the first 2 weeks not progressing in frequency, volume, or intensity to allow adaptations to the addition of strength training. Following the first two weeks of the trial, weekly running volume will be progressed between 10% and 30% depending on the run training history, time availability, running goals and symptom behaviour of each participant. Weekly running progressions will be programmed and discussed with [name] at week two and week four follow up sessions to ensure an appropriate progression of load for each participant. Participants' running intensity will not be able to exceed a moderate intensity, rated as 6 out of 10 on an 11‐point Borg Scale (0–10) (“labored breathing, challenging and uncomfortable, but sustainable for 30–60 min”) throughout the duration of the trial [15]. Running intensity will be discussed with [name] and details included in weekly run program progressions. If participants experience an exacerbation of their symptoms following a run, they are to report this to [name] and rest until their symptoms have returned to ‘usual’ levels before running again. Their next run is to be completed at an intensity no greater than 4 out of 10 on an 11‐point Borg Scale (“still comfortable, able to hold a conversation”) [15]. If participants experience an exacerbation of their symptoms post‐run over two consecutive run sessions, they are to contact [name] and a modification to their running program will be discussed based on both the severity and time of onset of their symptoms.

The following criteria will be used to guide the progression of each participants running load:(i)volume will be programmed in minutes; with weekly progressions not exceeding 30%(ii)intensity will be programmed using rate of perceived exertion (rate of perceived exertion (RPE)) and rated using an 11‐point Borg Scale (0–10) [15]; intensity minutes will be calculated (*RPE  x minutes*) and monitored, with weekly progressions not exceeding 30%(iii)frequency can be progressed, provided volume progressions do not exceed 30%(iv)terrain is not to be progressed, and participants are to continue to run on their usual terrain (i.e., surface, elevation etc.)

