### Session 1 (baseline)

2.9

A clinical examination will be performed to ensure that participants have a clinical diagnosis of MTSS [2]. Participants will complete a questionnaire to obtain information concerning the presentation of their symptoms (lower limb affected, duration of symptoms). Participants' age, sex, gender, height, and mass will be recorded. Data regarding running participation (current running volume, running training history) will also be obtained. During the baseline assessment, participants will have primary and secondary outcome measurements (see ‘outcome measures’ section for details regarding all outcomes) collected prior to being allocated to their intervention.

Participants will receive the first 2 weeks of their strengthening program, with exercises demonstrated by [name] ([name]). Participants will then be supervised completing each exercise to ensure appropriate technique and safe execution of the program. Instructions regarding the determination of exercise dosage will be given. Participants will be provided with a Garmin running watch for the duration of the trial if they do not own one that meets the needs of the study. Participants in both groups will have 2D video footage of their running collected. Participants allocated to the intervention group will be receive a running retraining intervention to reduce their running step length, and a step rate target for overground running will be determined. The target step rate will be programmed into participants Garmin watch to enable real‐time feedback. No further instructions will be provided to participants allocated to the control group; however, they will be instructed that we will be documenting how their running mechanics change throughout the duration of the trial.

Participants will be instructed on the use of software, as described previously, to record adherence with their strengthening program and how to document their symptom management strategies (e.g., ice, oral medications, etc.). They will also be given further information regarding the secondary outcome measure ‘worst pain experienced during a run’ to be recorded on a NPRS. Participants will discuss their current symptoms and run load with [name], and an appropriate run program for the first 2 weeks will be outlined.

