### Descriptive analysis

3.1

Differences between the control and intervention group in demographic and clinical characteristics and for the primary and secondary outcome measures (2, 4, and 8 weeks) will be described and assessed using *t* tests for continuous and chi‐square for categorical variables. If after assessment of the assumptions of the *t* test (such as the homogeneity of variance) are violated, we will use alternatives such as the Welch's test with Satterhwaite approximation as a sensitivity analysis. For cell counts <5, *p* values from chi‐square tests will not be reported.

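### Weekly run volume is programmed as a percentage of each runner's own volume but compared in raw km per week, with no stated use of the running volume collected before allocation: valid, but imprecise

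*Protocol article*

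**What the plan says.** - **Unit.** Section 2.14.5 of the protocol article totals each runner's watch distances: "Running volume will be recorded as kilometres per week".
- **Programme, both arms.** Section 2.6.1 starts from an individual run plan, "with the first 2 weeks not progressing in frequency, volume, or intensity to allow adaptations to the addition of strength training". After that, "weekly running volume will be progressed between 10% and 30% depending on the run training history" and other personal factors, with a ceiling of 30% a week. Volume can also fall: runs are limited by pain, and after a flare-up the runner must "rest until their symptoms have returned to" usual levels.
- **Simple comparison.** Section 3.1 applies t tests to continuous variables, covering the "primary and secondary outcome measures (2, 4, and 8 weeks"). It states no change score, ratio or baseline term.
- **Model.** Section 3.2 adds a mixed effects model. It names age, sex, BMI, symptom management and footwear as examples of fixed effects, and promises other modelling if normality or equal variance fails.
- **Baseline.** Section 2.9: "Data regarding running participation (current running volume, running training history) will also be obtained". The same section has outcome measurements taken before allocation. Randomisation is stratified by sex at birth only (section 2.1).

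**The concern.** Volume under this programme is the runner's own starting volume multiplied by a growth factor. If retraining lets runners tolerate faster progression, the effect is a ratio to their own start. A t test on raw km sets that ratio against the whole spread in how much people ran before the trial. Eligibility asks for at least two runs a week and sets no upper limit on volume, so that spread is likely to be wide.

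The stake is a false null on an outcome that the article's background treats as important: it says clinicians and runners want less lost running volume and a quicker return to usual volume. The variable that would remove most of the unwanted spread is already being collected.

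**Working it through.** **The plan's own figure.** The only sample size is for the UWRI. With d = 5/6.7 = 0.746, two-sided α = 0.05 and 80% power, the exact two-sample t calculation gives 30 per arm, or 60 in total, as stated. The article gives no SD, effect or power for run volume, so every run-volume input below is an assumption except the 32 per arm and the programme rules.

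**Growth the programme allows.** Taking two weekly progressions by week 4 and six by week 8:
- week 4: 1.1² = 1.21 to 1.3² = 1.69 times the start
- week 8: 1.1⁶ = 1.77 to 1.3⁶ = 4.83 times the start

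**Assumptions for power.** Mean start 25 km/week; baseline CV 30–60%; SD of weekly progression between runners 6 points; week-to-week noise 20%; error in the baseline figure 15%; mean weekly progression 10% v 20%.

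**Hand check at week 4, CV 50%, on the log scale.** log(volume) = log(start) + 2·log(1+g) + noise.
- Effect: 2·ln(1.20/1.10) = 0.174, a ratio of 1.44/1.21 = 1.19.
- Variance from starting volume: ln(1 + 0.5²) = 0.223. From noise: 0.2² = 0.040. From progression: (2 × 0.06/1.15)² = 0.011.
- Ignoring baseline: SD = √(0.223 + 0.040 + 0.011) = 0.523 and d = 0.174/0.523 = 0.333. The noncentrality is 0.333 × √(32/2) = 1.33, so power ≈ Φ(1.33 − 2.00) ≈ 25%. Starting volume is 0.223/0.274 = 81% of the variance.
- Relative to baseline measured with 15% error: SD = √(0.040 + 0.011 + 0.0225) = 0.271 and d = 0.642. The noncentrality is 2.57, so power ≈ Φ(0.57) ≈ 72%.

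**Simulation on the same assumptions.**

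| Comparison | Raw-km t test | Km with baseline covariate | Log or ratio scale |
|---|---|---|---|
| Week 4, 10% v 20%, CV 30–60% | 18–42% | 60–68% | 70–74% |
| Week 8, 12% v 18%, CV 40–60% | 37–60% | 74–80% | 86–88% |

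At CV 30%, week 8 gives 69% on raw km against 87% on the ratio scale. Type I error is about 5% for the raw-km t test and for the log-ratio t test.

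**Share of log-volume variance due to starting volume**, in a separate set of runs with progression inside 10–30% and baseline CV 30–70%:

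| Weekly noise | Week 2 | Week 4 | Week 8 |
|---|---|---|---|
| 10% | 0.90–0.98 | 0.82–0.96 | 0.48–0.84 |
| 25% | 0.58–0.86 | 0.55–0.85 | 0.41–0.76 |

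**Less favourable inputs (week 4).** Confining progression to 10–30% lowers log-ratio power from about 72% to 51–52%. Adding 10% zero-km weeks leaves a log-link model at 22–23%, against 9–14% for raw km. With 18% v 22% and 25% noise, power is 6–10% on raw km and 17–18% relative to baseline.

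**The case against.** The strongest reply is that the quoted sentence fixes a recording unit, not an analysis scale, and that section 3.1 is headed as descriptive. The group estimates come from the mixed model. Its covariate list is illustrative, it allows other modelling when assumptions fail, and it could take in the baseline measurements. A condensed article may leave covariates for one secondary outcome to a fuller plan. All of this stands against any claim that baseline volume is ruled out. It does not change the fact that the one between-group test tied to named visits has no baseline term and fits the programme poorly.

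Three stronger readings are tempting but unsupported.

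- **That the test measures who ran more before the trial, so a chance imbalance gives a biased result.** Starting volume is randomised and the raw test's type I error is about 5%. The loss is of precision. At week 8 with a baseline CV near 30%, starting volume need not even be the larger part of the spread.
- **That week 2 is fixed by instruction and so uninformative.** Section 2.6.1 rules out progression but does not hold volume up. Pain limits and rest can lower it, and they could do so differently by arm.
- **That the measurement scale is the main fault.** Keeping km and adding baseline as a covariate recovers most of the lost week-4 power; the ratio scale adds a smaller further gain.

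**Conclusion.** The concern holds as a matter of efficiency. A raw-km comparison of weekly run volume is valid but imprecise. On the stated assumptions, using the pre-allocation volume raises week-4 power from about 18–42% to 60–68%, and the log or ratio scale takes it to 70–74%. The absolute levels depend on assumed inputs and fall for every method if progression stays within 10–30% or if zero-km weeks occur. The ordering held in every week-4 and week-8 scenario where raw km left room for gain. At week 2 no method gains in these models, because neither arm progresses. This is one secondary outcome; the UWRI analysis and the sample size of 60 do not depend on it.

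**What to change.** In the analysis section, state that weekly run volume will be analysed with pre-allocation running volume as a covariate, preferably on a ratio scale. Use log volume with log baseline volume as covariate or, if zero-km weeks occur, a log-link model reported as a ratio of means. Present km per week alongside.

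The log-link model needs small-sample-corrected robust standard errors. With ordinary robust errors at 32 per arm, its simulated type I error was roughly 5.6–7.6%.

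Name weeks 4 and 8 as the comparisons of progression. Report week 2 as the phase in which programmed volume cannot rise but can fall, so that any difference there is read as a difference in reductions.

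The cost is one paragraph of wording and no new data. The drawbacks are that baseline volume may be self-reported, and that a ratio is less immediate to readers than km.

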#### Reactive strength index score

2.14.6

Reactive strength index (RSI) is a ratio score that provides a measurement of a person's ability to produce force rapidly and represents an individual's ability to effectively utilise the stretch‐shortening cycle. This typically occurs in movements where body segments are exposed to impact forces that induce stretch (i.e., ground contact when running) [20]. RSI score has been associated with both isometric strength and endurance performance and is calculated by dividing either jump height or flight time by ground contact time and has shown moderate to strong levels of reliability (ICC 0.57—0.99; coefficient of variation 2.98%—14%) across a range of populations [20]. RSI will be assessed on force decks (Force Decks, Vald Performance, Queensland, Australia) using a drop jump to a standardised height of 30 cm [20], and the measurement taken from flight time and contact time data. Participants will initially stand with one foot on each force deck to allow calibration, they will then be instructed to stand on a 30 cm box placed behind the force decks, keeping their posture upright and their eyes forward. When ready, they will be instructed to step off the box (stepping out and not down) to ensure the drop height remains 30 cm, landing on both legs at the same time before immediately jumping as high as possible with the shortest possible contact time with the ground. RSI scores will be calculated using the following equation:

$$Reactive\;strength\;index\;\left(RSI\right)=\frac{Flight\;time\;\left(ms\right)}{Contact\;time\;\left(ms\right)}$$

#### Single leg hop test

2.14.7

A single leg repetitive hop test will be used to obtain a measure of vertical stiffness for both limbs. The testing of repeated single leg vertical hops measured on portable force plates has been shown to be reliable in a healthy athletic population (ICC ≥0.97) [21]. Participants will be instructed to stand on force decks (Force Decks, Vald Performance, Queensland, Australia) whilst they are calibrated. They will then be instructed to place their hands on their hips and hop continuously on one leg whilst minimising contact time for 10 hops. The hopping test will be performed on both left and right sides. RSI scores will be calculated from the hop flight and contact times as previously described, and data from the best five hops on each leg will be used.

#### Maximum voluntary isometric contraction—soleus (single leg)

2.14.8

Previous research has found symptomatic runners with MTSS to have reduced ankle plantar flexor muscle endurance [22, 23]. Both studies evaluated plantar flexor muscle endurance measures with a standing heel‐raise test. Mattock and colleagues also assessed maximal voluntary isometric contraction (MVIC) strength of flexor hallucis longus, flexor digitorum, soleus, peroneal tibialis anterior and soleus muscle, measured with a hand‐held dynamometer and found significant strength deficits in flexor hallucis longus, peroneal, soleus and tibialis anterior [23]. We will be testing MVIC with the use of force decks (Vald Performance, Queensland, Australia). Use of force deck to test the isometric strength of soleus has been reported to be reliable in a population of elite footballers [24]. Participants will be seated in a position that ensures a testing bar height with participant's hip and knee at 90° flexion. The foot being tested will be placed in the centre of the force plate and in a position that has the ankle at 90° dorsiflexion. Force decks will then be calibrated with participants in the appropriate testing position. Participants will be advised to maintain a neutral foot position and apply minimal pre‐tension on the bar until the verbal instruction is given to commence the test. Before each repetition, the participant will be guided by a countdown (“3, 2, 1”) and instructed to push for 3 seconds up and against the bar as hard and as fast as possible [24]. Three repetitions will be conducted, with data representing the best of the three trials. Maximal voluntary isometric contraction will be represented as peak force in newtons per kilogramme.

#### Maximum voluntary isometric contraction—gastrocnemius (single leg)

2.14.9

Following warm‐up and familiarisation, participants will be instructed to stand with their tested leg in the centre of the force deck (Force Decks, Vald Performance, Queensland, Australia), in this position force decks will be calibrated prior to commencing testing. Bar height will be determined to ensure participants knee is in an extended position (0° flexion), this will be confirmed with a goniometer. Foam padding (Iron Edge, Melbourne, Australia) will be placed around the testing bar to ensure comfort on participants' shoulders and upper back during the test. Participants will be advised to apply minimal pre‐tension on the bar until the verbal instruction is given to commence the test. Before each repetition, the participant will be guided by a countdown (“3, 2, 1”) and instructed to push for 3 seconds up and against the bar as hard and as fast as possible [24]. Three repetitions will be conducted, with data representing the best of the three trials. Maximal voluntary isometric contraction will be represented as peak force in Newtons per kilogram.

#### Plantar flexor endurance test (single leg)

2.14.10

Plantar flexor endurance will be measured using the standing heel‐rise test. This test has been shown to be reliable in healthy populations (ICC 0.79—0.96), but to our knowledge has not been assessed for reliability in people with MTSS [22]. Following warm‐up and familiarisation, participants will be required to perform as many single leg calf raises as possible. Participants will start standing with their forefoot on the edge of a box, with index and middle fingertip support from both hands on the wall at shoulder height for balance permitted. They will be required to maintain the knee of their tested leg straight (extended) during testing. Participants will be asked to stand on one foot and raise the heel of their ipsilateral limb as high as possible so a string line can be placed contacting the proximal dorsal aspect of the foot to identify the target height of a complete repetition. Participants will then be instructed to raise and lower their heel to the beat of a 60 Hz metronome, lifting their heel as high as possible to contact the string line in one beat and lowering it in one beat (i.e., 30 calf raise repetitions per minute). Participants will be encouraged to go through the full range of available motion. The test will be terminated once participants are no longer able to perform a repetition, cannot maintain the beat of the metronome, demonstrate compensatory movements (e.g., knee flexion, trunk lean, hip strategy), or show marked reduction in heel range of motion. Two minutes rest will be allocated between legs [25]. Scores will be represented as number of single leg calf raises.

